### Participant timeline

The study will be implemented from March 2020 to June 2024, allowing for three years of interventions. Participants will be met on one or two subsequent days, for consenting, questionnaires and urine collection and examination. Figure 5 shows the timeline of surveillance-response activities in low-prevalence IUs and of the multi-pronged interventions in hotspot IUs.

**Fig. 5 Fig5:**
[figure not shown]
Timeline of interventions against urogenital schistosomiasis in the 20 SchistoBreak study shehias in Pemba, Tanzania. IU: implementation unit

### Sample size

We run a series of simulations to assess how precisely the sensitivity of the surveillance system can be estimated. We modelled different scenarios with varying prevalences in schoolchildren as well as in the general population, different values for clustering and different assumptions for diagnostic test accuracy and surveillance system performance. The results revealed that sampling an average of 140 schoolchildren and 250 community members in each of 15 low-prevalence shehias in the cross-sectional surveys enables us to estimate the prevalence with a median precision (defined as one half length of the confidence interval) of 10 to 15 percentage-points in schoolchildren and of 5 to 7 percentage-points in the general population. The bias (defined as difference between the sensitivity calculated using the apparent prevalence observed during cross-sectional surveys and the sensitivity calculated using the "true" apparent prevalence observed during the surveillance activities) had a median of zero and an interquartile range from − 0.05 to 0.05.

Hence, conducting the cross-sectional surveys in the schools and communities of all 20 study shehias, the yearly total sample is 7800 individuals (ca. 10% of the population, based on an average of 4000 inhabitants per shehia).

In addition, during the surveillance activities in 15 low-prevalence shehias, we roughly estimate to test annually about 12,150 individuals (ca. 20% of the population). Among them, around 7500 will be subjected to active surveillance in high-risk schools (estimated n = 15 shehias*1 school*450 children + estimated n = 15 shehias*1 school*50 children = 7500 samples per year), 750 to reactive surveillance in households (estimated n = 15 shehias*10 households*5 inhabitants = 750 samples per year) and 1500 at mobile test-and-treat stalls (estimated n = 15 shehias*10 water bodies *10 people = 1500 per year), and 2400 to passive surveillance in health facilities (estimated n = 20 health facilities*12 months*10 patients = 2400 samples per year).

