### Interventions and data collection

In the study, specific intervention packages will be tailored and adapted to the local micro-epidemiology of urogenital schistosomiasis in the shehias. Low-prevalence IUs will receive tailored surveillance-response measures, consisting of active, passive and reactive case finding, treatment of *S. haematobium*-positive individuals and focal snail control. Hotspot IUs will receive a multi-disciplinary intervention package including MDA, snail control and behaviour change communication. The classification of the study shehias into low-prevalence or hotspot IUs will be based on the results of annual cross-section surveys. Initially, a shehia will be considered a low-prevalence IU if it shows an apparent *S. haematobium* prevalence < 2% in the community-based survey and an apparent *S. haematobium* prevalence < 3% in the school-based survey, based on single urine filtration microscopy. Otherwise, the shehia will be considered a “hotspot” IU (Fig. 3). Results gained over the study period will show whether these thresholds and respective intervention packages successfully sustain and accelerate the gains and prevent recrudescence of *S. haematobium* transmission in low-prevalence IUs. The thresholds will be evaluated annually in light of the results of the cross-sectional surveys and adapted if needed.

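### The sample-size section gives the prevalence a confidence-interval half-width of 10–15 and 5–7 percentage points, which does not fit the stated samples at prevalences of at most 3%

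*Protocol article*

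**What the plan says.** The Sample size section opens with its purpose: "We run a series of simulations to assess how precisely the sensitivity of the surveillance system can be estimated". It then describes the design as "sampling an average of 140 schoolchildren and 250 community members in each of 15 low-prevalence shehias". For the school sample, this is said to allow "us to estimate the prevalence with a median precision (defined as one half length of the confidence interval) of 10 to 15 percentage-points". The second figure it reports is a half-width "of 5 to 7 percentage-points in the general population". The next sentence turns to bias, defined as a difference between two versions of the sensitivity; this "had a median of zero and an interquartile range from" −0.05 to 0.05. The yearly survey total of 7,800 is presented as following from these results.

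The section Interventions and data collection defines a low-prevalence shehia by two conditions on single urine filtration: "prevalence < 2% in the community-based survey" and "prevalence < 3% in the school-based survey". The Discussion gives the two thresholds the other way round. Those passages need reconciling, but under either version the ceiling is at most 3%.

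Statistical methods defines the primary outcome as one overall sensitivity: detected cases divided by an estimated number infected. That number is the sum of a school and a non-school term, each a prevalence times a population size. The prevalences and their intervals come from generalized estimating equations (GEE) with an independence working correlation.

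**The concern.** A half-width of 10–15 points around a prevalence of 3% or less is 3.3 to 5 times the prevalence itself (10/3 and 15/3). For the community, 5–7 points around 2% is 2.5 to 3.5 times. Samples of 2,100 and 3,750 should do far better.

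The section also changes subject. Its aim and its bias sentence concern the sensitivity of the surveillance system, and only the precision sentence names the prevalence.

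The precision and bias sentences are the only quantitative support for the sample size. The Discussion concedes that the study is underpowered for changes in prevalence and adopts sensitivity as primary outcome for that reason. So the half-width that matters most is that of the sensitivity, and no half-width is given under that name. Taken literally, the sentence also says that the survey prevalences, which form the denominator of the primary outcome, are almost uninformative.

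**Working it through.** **Inputs from the protocol article.** Sample size: 140 schoolchildren and 250 community members per shehia, 15 shehias, so n = 2,100 and n = 3,750. Interventions and data collection: ceilings of 3% (school) and 2% (community).

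**Assumptions.** The confidence level is not stated; 95% is used. The clustering values are not stated; ICCs from 0 to 0.10 are shown, with 1 as the extreme.

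**Formula.** Half-width = 1.96 × √(p(1−p)·DE/n), where DE = 1 + (m−1)·ICC and m is 140 or 250.

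Without clustering:
- School: 1.96 × √(0.03 × 0.97/2,100) = 0.0073, or 0.73 points.
- Community: 1.96 × √(0.02 × 0.98/3,750) = 0.0045, or 0.45 points.

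With clustering, multiply by √DE:

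| ICC | School DE | School, 3% | Community DE | Community, 2% |
|---|---|---|---|---|
| 0 | 1 | 0.73 | 1 | 0.45 |
| 0.01 | 2.39 | 1.13 | 3.49 | 0.84 |
| 0.05 | 7.95 | 2.06 | 13.45 | 1.64 |
| 0.10 | 14.9 | 2.82 | 25.9 | 2.28 |
| 1 | 140 | 8.6 | 250 | 7.1 |

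**Attempt to reproduce the stated figures.** Solve for the design effect needed:
- School, 10 points: (10/0.73)² ≈ 188. School, 15 points: about 423. The maximum for clusters of 140 is 140, so neither can be reached at 3%.
- Community, 5 points: (5/0.448)² ≈ 125, ICC = 124/249 ≈ 0.50. Community, 7 points: about 244, ICC = 243/249 ≈ 0.98.
- With the thresholds swapped as in the Discussion, 10 points in schools at 2% needs a design effect of 279, again above 140. The community at 3% needs an ICC of 0.33 to 0.66.

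**Other readings tried.**
- One shehia alone, by Wald, Wilson and Clopper-Pearson intervals: 2.8–3.2 points (n = 140, 3%) and 1.7–2.0 points (n = 250, 2%).
- One shehia alone at 50% prevalence: 8.3 points (n = 140), still short of 10, and 6.2 points (n = 250), which is inside 5–7 but far from a low-prevalence setting.
- A beta-binomial simulation with 15 clusters, 4,000 runs and the robust standard error of the planned GEE, at prevalences of 0.5–3% and ICCs of 0.01–0.10: median half-widths of 0.4–2.5 points in schools and 0.3–2.4 in the community.

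No reading at low prevalence gives the printed values under moderate clustering.

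**Could the figures be the precision of the sensitivity?** Sensitivity is detected cases over P × N, so by the delta method its half-width is about sensitivity × (half-width of P)/P.
- School, assumed sensitivity 0.4, prevalence 3%: 0.4 × 0.73/3 = 9.7 points at ICC 0; 0.4 × 1.13/3 ≈ 15.0 points at ICC 0.01.
- Community, assumed sensitivity 0.2, prevalence 2%: 0.2 × 0.448/2 = 4.5 points at ICC 0; with DE = 1 + 249 × 0.005 = 2.245, 6.7 points at ICC 0.005.

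The printed sizes are thus attainable for a sensitivity. The inputs were chosen to illustrate this, and others give quite different results: school sensitivity 0.4 at 1% prevalence and ICC 0.05 gives 48 points.

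**The case against.** **The simulations varied the prevalence.** The 3% ceiling is defined on single urine filtration, and the section says that prevalences and test accuracy were varied without giving values. At an assumed 5% prevalence and an ICC of 1, the school half-width is 1.96 × √(0.05 × 0.95 × 140/2,100) ≈ 11 points. The word unattainable therefore holds only at the stated ceilings. The community figure is very implausible but not impossible. Both limits stand, but neither makes the printed sentence credible for low-prevalence shehias.

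**Only a noun may be wrong.** Sample sizes, estimator and analysis would then stay as they are, and a condensed article may leave simulation inputs to a fuller document. The absence of those inputs is not held against the article. A specific printed figure that does not fit its named quantity remains an error.

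**Stronger readings that the document does not support.**
- A reader might take it as established that the figures belong to the sensitivity. The section's aim, its bias sentence and the size of the numbers favour this, but without the inputs it is an inference.
- A reader might convert the bias interquartile range of ±0.05 into a half-width: 0.05/0.6745 × 1.96 ≈ 14.5 points. This assumes normality, may mix scenarios, and matches only the school figure; 5–7 points would imply about ±0.017 to ±0.024. The range does give some information on the error in the sensitivity, so the section is not silent on it.
- A reader might conclude that classification at 2% and 3% is undermined. Classification is made shehia by shehia on apparent prevalence, so an interval pooled over 15 shehias does not govern it.
- A reader might want fixed replacement ranges for the prevalence. These depend on the clustering, which the article does not state.

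**Conclusion.** The sentence is wrong as written. In schoolchildren the stated precision is about 14 to 20 times the unclustered value (10/0.73 and 15/0.73) and 3.5 to 5.3 times the value at an ICC of 0.10 (10/2.82 and 15/2.82). In the community it is about 11 to 16 times the unclustered value (5/0.448 and 7/0.448) and 2.2 to 3.1 times the value at an ICC of 0.10 (5/2.28 and 7/2.28). This rests on a 95% level, the stated samples, and prevalences at the low-prevalence ceilings; lower prevalences narrow the intervals further.

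That the figures describe the sensitivity is the likeliest explanation, not a demonstrated one. Even if confirmed, it would leave a gap. The primary outcome is one overall sensitivity whose denominator adds school and non-school infections, and separate figures for schoolchildren and the general population are not the precision of that quantity. The error concerns the justification of the sample size; it does not show that the sample is too small.

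**What to change.** Check the simulation output and correct the sentence in one of two ways:

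- If the half-widths are those of the surveillance sensitivity, name that as the quantity and give the sensitivity, prevalence and clustering scenarios behind the 10–15 and 5–7 points.
- If the prevalence was meant, replace the figures with the prevalence half-widths actually obtained at the clustering values simulated.

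In either case, add the expected half-width of the overall sensitivity as defined in Statistical methods, and state the confidence level. The correction is one or two sentences from existing output. The overall figure may need one further summary of the same simulations. No change to the sample, the fieldwork or the analysis follows from this point.

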### Primary and secondary objectives

The primary objective of this study is to quantify the sensitivity of an adaptive surveillance-response approach for its ability to detect *S. haematobium* infected individuals in low-prevalence areas to trigger an appropriate intervention response. The primary outcome variable will be the number of *S. haematobium* infected individuals detected and reported through the surveillance approach divided by the number of positive individuals in the population as extrapolated from the cross-sectional surveys, i.e. the mean sensitivity of the surveillance-response approach determined over 3 years.

Secondary outcome analyses will cover additional performance parameters of the surveillance approach, as defined by WHO [45]. Moreover, we will assess the impact of multi-disciplinary interventions in hotspot areas, as well as the coverage of test-and-treat activities in low-prevalence areas and of MDA in hotspot areas. Other secondary outcomes will include the accuracy of several diagnostic approaches and micro-mapping of characteristics of the study shehias, including the number and location of schools, madrassas (Islamic schools), and health facilities, the number and location of water bodies and the abundance of intermediate host snails of the genus *Bulinus*.

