Both, reagent strip and urine filtration methods are not very sensitively detecting light intensity infections, as they might occur frequently in people living in elimination settings such as Pemba [29]. Hence, 10 ml from each urine samples collected at the baseline and endline survey will be stored at -20 °C and examined with a highly sensitive and specific test at the end of the study. This might be a DNA-based PCR approach [31] or an antigen-based test such as the up-converting phosphor-lateral flow circulating anodic antigen (UCP-LF) CAA assay [30] or any other test with excellent parameters developed until 2024.

To increase the performance of our surveillance-response approach, ideally a PoC test with a higher sensitivity and specificity than the reagent strips will be used. No such tests are yet (in 2021) commercially available, but several are under development. In the SchistoBreak project, we will investigate the performance of new rapid diagnostic tests, such as the Recombinase Polymerase Amplification (RPA) assay [44, 60], or other DNA-based, antigen-based or egg-based diagnostic tests for *S. haematobium* diagnosis at the PoC during our cross-sectional and surveillance activities. Once validated, applicable at the PoC, and available and affordable in sufficient numbers to screen our participants, promising candidates might be applied throughout the cross-sectional surveys and surveillance activities of the SchistoBreak project.

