### Statistical methods

To analyse the primary outcome, we define the sensitivity of the surveillance system as the proportion of cases detected:$${\text{SE}} = {\text{N}}_{{{\text{inf detected by surveillance}}}} / {\text{N}}_{{{\text{inf}}}}$$

The total number of infected persons is unknown but will be estimated from the cross-sectional surveys as:$${\text{N}}_{{{\text{inf}}}} = {\text{ P}}_{{{\text{school}}}} *{\text{ N}}_{{{\text{school}}}} + {\text{ P}}_{{{\text{non}} - {\text{school}}}} *{\text{ N}}_{{ {\text{non}} - {\text{school}}}}$$whereby prevalences (P) and corresponding confidence intervals are estimated via generalized estimating equations for binary data with independent correlation structure to account for correlation within clusters.

The prevalence and intensity of *S. haematobium* infections will be calculated by different diagnostic approaches used in the annual cross-sectional surveys. Intensity of infection will be classified into light (< 50 eggs/10 ml urine) and heavy (≥ 50 eggs/10 ml urine) according to thresholds provided by the WHO for urine filtration results [3].

The timeliness of case notification and reactive intervention will be assessed by recording the time needed from diagnosis to treatment, from diagnosis to follow-up of *S. haematobium* positive individuals and test-and-treat of their household members, and from diagnosis to reactive snail control.

The acceptability of the surveillance-response approach will be assessed by a mixed methods approach based on the results of questionnaires run in parallel to test-and-treat approaches in low-prevalence shehias.

The coverage of test-and-treat activities will be calculated by assessing the number of people who were targeted by test-and-treat activities in relation to the total population.

MDA coverage will be calculated by assessing the number of people reporting in the cross-sectional surveys that they received praziquantel during the last MDA in relation to the total number of participants in the cross-sectional surveys.

MDA compliance in hotspot areas will be calculated by assessing the number of people reporting in the cross-sectional surveys that they have taken praziquantel as recommended, in relation to the total number of participants in the cross-sectional surveys.

The impact of snail control will be determined by assessing the snail abundance and number of intermediate host snails at each HWCS identified over time during regular snail surveys.

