## Discussion

In the new WHO Roadmap on NTDs published in 2021, the global elimination of schistosomiasis as a public health problem and the validated absence of infections in humans in 25 among 78 endemic countries is set as target for 2030 [5]. To achieve these goals, countries and their schistosomiasis programme managers will need clear guidance on which intervention strategies to apply, which population groups to target, which diagnostics to use, and at what thresholds to change and adapt their strategies [11–13]. In Zanzibar, which is committed to eliminate urogenital schistosomiasis in the next years, a long-term study conducted from 2012 to 2020, revealed considerable temporal and spatial heterogeneity of *S. haematobium* infections that will need to be considered in future intervention planning [6, 17, 18]. Within the SchistoBreak study we will address the focality and heterogeneity of *S. haematobium* transmission in Pemba and aim to investigate novel adaptive intervention strategies as well as standard and new diagnostic tools for schistosomiasis elimination in Zanzibar.

Working in an elimination setting, however, there are foreseeable challenges for analyses and implementation:

First, most of the population in our study area is free of schistosomiasis and there will only be very few *S. haematobium* infected individuals. Hence, even with a very large sample size involving several thousand participants, the study is underpowered and we will most likely not be able to determine the impact of our interventions in terms of statistically significant differences in the *S. haematobium* prevalence assessed in annual cross-sectional surveys. Therefore, as a computable and meaningful primary outcome, we will assess the sensitivity of the surveillance approach, based on the number of *S. haematobium* cases detected by active, reactive and passive surveillance in schools and communities divided by the total number of infected persons estimated from the cross-sectional surveys.

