Second, the urine filtration and reagent strip methods that we will apply for the standard diagnosis of *S. haematobium* infection markers are not very sensitively and specifically detecting light intensity infections as primarily found in Zanzibar [29–31, 61]. Hence, in cross-sectional surveys, as well as in the surveillance-response approach, we will likely miss a considerable number of *S. haematobium-*positive individuals and underestimate the “true” prevalence. Clearly, our surveillance system will only be as good as the diagnostic methods employed. The undetected false-negative cases missed due to low test sensitivity might act as a reservoir for infections and contribute to continuous transmission. The false-positive individuals indicated by low test specificity will be chased for nothing and valuable resources and time will be wasted [13]. To improve the surveillance and get a more realistic picture of the “true” prevalence in cross-sectional surveys, in addition to the standard methods, we will apply DNA-based or antigen-based diagnostic tests, at least for the examination of urine samples at baseline and endline and, once readily available and validated, at the PoC during surveillance.

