Despite the highlighted challenges, the SchistoBreak study will fill a critical health knowledge gap and produce important and much needed results. The study will show whether the performance of surveillance-response as intervention in low-prevalence IUs is sufficiently high to detect successfully all urogenital schistosomiasis cases and to respond with adequate interventions so that recrudescence of transmission can be prevented. It will also reveal if the *S. haematobium* prevalence in hotspot IUs can be reduced to very low levels when a comprehensive, multi-disciplinary intervention package is applied. Finally, the study will show whether new diagnostic tests are suitable for application at the PoC and outperforming current standard tests in their sensitivity and specificity to detect *S. haematobium* infections. Hence, our study will shed light on the field applicability and performance of novel adaptive intervention strategies and new diagnostic tools for schistosomiasis elimination and reveal whether progress towards interruption of transmission can indeed be achieved and sustained in the suggested way. The evidence and experiences generated by micro-mapping of *S. haematobium* infections at sub-district community level, micro-targeting of different intervention approaches, and application of novel diagnostic tools can guide future strategic plans for schistosomiasis elimination in Zanzibar and inform other countries aiming for interruption of transmission.

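### The zero median bias in the sample-size simulation is measured against test-positive persons, so it does not describe error in the sensitivity among infected persons on which the article concludes

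*Protocol article*

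**What the plan says.** The Sample size section describes simulations that varied prevalence, clustering, diagnostic accuracy and surveillance performance. It defines its bias term as follows: "The bias (defined as difference between the sensitivity calculated using the apparent prevalence observed during cross-sectional surveys", minus the sensitivity computed with the so-called true "apparent prevalence observed during the surveillance activities) had a median of zero". The interquartile range is −0.05 to 0.05.

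The denominator of the primary ratio is named in three places:
- Primary and secondary objectives: the "number of positive individuals in the population as extrapolated from the cross-sectional surveys".
- Statistical methods: "The total number of infected persons is unknown but will be estimated from the cross-sectional surveys as", followed by a formula that sums prevalence times population size for the school and non-school groups. No correction for test accuracy is stated, and the formula does not name the test that supplies the prevalences.
- Discussion, first challenge: detected cases are "divided by the total number of infected persons estimated from the cross-sectional surveys".

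On test accuracy, the Discussion says that "in cross-sectional surveys, as well as in the surveillance-response approach, we will likely miss a considerable number of" positive individuals, and that the true prevalence will be underestimated. Laboratory procedures and data collection plans a more sensitive test: "10 ml from each urine samples collected at the baseline and endline survey will be stored" and examined at the end of the study. Nothing links that test to the primary ratio. The closing part of the Discussion says the study will show whether surveillance performance "is sufficiently high to detect successfully all urogenital schistosomiasis cases".

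**The concern.** A bias statement in a sample-size section is normally read as a property of the primary estimator. Here the estimate and its benchmark are both built on apparent prevalence. If a test misses infections, they are missing from both terms, and the difference cannot show the effect, even though test accuracy was one of the inputs varied.

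The documents then use two names for the denominator. If it is test-positive persons, the benchmark is coherent. If it is infected persons, the benchmark is the wrong one, and the article's own expectation of missed infections means that the uncorrected ratio may differ materially from the quantity named. At stake is how the headline sensitivity is read: as the share of test-positives that surveillance finds, or as the share of infected people. A statement about detecting all cases needs the second.

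**Working it through.** **Reproducing the stated figure.** The simulation inputs are not printed, so an exact reproduction is impossible. A Monte Carlo check (1,500 runs per scenario) used the article's 15 low-prevalence shehias of 4,000 people with 140 schoolchildren and 250 community members sampled in each. The following are assumptions, not document values: 25% of the population in school, surveillance reaching 50% of school and 12% of non-school infections, true prevalence 3%/2% or 1.5%/1% (school/non-school), intracluster correlation 0 to 0.02, and test sensitivity s from 0.4 to 1.0. Against the apparent benchmark the median bias was 0.00 in every scenario, including those with imperfect specificity. The interquartile half-width ran from about 0.01 to 0.07, which spans the stated 0.05.

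**Why the median is zero whatever s is.** Let N be the number truly infected and c the fraction of them reached and tested by surveillance. With the same test on both sides and specificity 1:
- detected = c·s·N
- survey-based denominator = s·N
- reported ratio = c·s·N / (s·N) = c
- sensitivity among infected persons = c·s·N / N = c·s
- difference = c·(1 − s); factor = 1/s

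The apparent benchmark also equals c, so s cancels.

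**Size with specificity 1.** For s = 0.8 the factor is 1/0.8 = 1.25; for s = 0.5 it is 1/0.5 = 2. A reported 20% corresponds to 0.20 × 0.8 = 16% down to 0.20 × 0.5 = 10%. A reported 40% corresponds to 32% down to 20%.

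The simulation agrees. Per shehia at 3%/2%, infected persons are 1,000 × 0.03 + 3,000 × 0.02 = 90. Those reached are 0.5 × 30 + 0.12 × 60 = 22.2, so c = 22.2/90 = 0.247.

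| s | median reported | among infected | bias vs infected | bias vs apparent benchmark |
|---|---|---|---|---|
| 1.0 | 0.25 | 0.25 | 0.00 | 0.00 |
| 0.8 | 0.25 | 0.20 | +0.05 | 0.00 |
| 0.6 | 0.25 | 0.15 | +0.10 | 0.00 |
| 0.4 | 0.25 | 0.10 | +0.15 | 0.00 |

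**Effect of false positives (same setting, 3%/2%).**
- Survey specificity 0.99, surveillance specificity 1, s = 0.8. Survey prevalences become 0.8 × 0.03 + 0.01 × 0.97 = 0.0337 and 0.8 × 0.02 + 0.01 × 0.98 = 0.0258. The denominator is 33.7 + 77.4 = 111.1 and the numerator 22.2 × 0.8 = 17.8. The ratio is 0.16 against 17.8/90 = 0.20, a bias of −0.04. With s = 0.5 it is +0.01.
- Both specificities 0.99: +0.04 (s = 0.8) and +0.11 (s = 0.5).
- Surveillance specificity 0.97, survey specificity 1: +0.40 (s = 0.8) and +0.69 (s = 0.5).

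Missed infections alone always push the ratio up. The net result depends on false positives on each side.

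**The case against.** The strongest reply is that the objectives define the denominator as positive individuals, the formula computes exactly that, and the simulation benchmark matches it. The Sample size section defines its bias term openly and uses the word apparent for both sides. The Discussion acknowledges missed cases in surveys and surveillance alike. This stands: no claim of unbiasedness for infected persons is hidden in the text, and on the test-positive reading the benchmark is sound. What remains is that Statistical methods and the Discussion name infected persons, and the closing statement concerns all cases.

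A second reply is that the simulation details are not shown. If the benchmark used the surveillance test (reagent strips, with filtration only on a subset), test error need not cancel exactly. That is fair, and is why the figure is said only mainly to reflect sampling error. In either case neither side counts infected persons.

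A reader might infer that the primary sensitivity is bound to be overstated. The documents do not support that. They describe the tests as imperfect in specificity as well as sensitivity, and they use different tests on the two sides. Under some assumptions the bias vanishes or turns negative.

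A reader might also infer that surveillance could score 100% and be wrongly declared complete. That is remote. The article expects to test about 12,150 of 60,000 people a year (20%), and a reported 20% or 40% says that not all cases are found, with or without correction. The classification of shehias follows survey prevalence thresholds, not this ratio.

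**Conclusion.** The point holds in a limited form. The median of zero and the interquartile range of ±0.05 describe error relative to test-positive persons. They say nothing about error relative to infected persons, which is the denominator named in Statistical methods and the Discussion. With perfect specificity, the same test on both sides and an assumed test sensitivity of 0.5 to 0.8 (the documents give no value), the uncorrected ratio is too high by a factor of 1.25 to 2. At a reported 20% that is 4 to 10 percentage points, against a stated half-width of 5. This error is systematic and does not shrink with more participants or with averaging over three years. Its net size and sign cannot be fixed from the documents, because specificity is not given and the tests differ between surveys and surveillance.

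**What to change.** 1. In Sample size, label the present figure as sampling error relative to test-positive persons. Also report the bias against truly infected persons over the test sensitivity and specificity values that the simulation already varies.
2. Reconcile Primary and secondary objectives, Statistical methods and the Discussion by calling the uncorrected ratio the share of test-positive persons detected.
3. For baseline and endline, report alongside it a ratio whose number of infected persons comes from the sensitive test already planned. Restrict it to the low-prevalence shehias, since infection intensity, and so test sensitivity, may differ in hotspots. Carry the uncertainty of that estimate into the interval. Limit the numerator to confirmed infections, or adjust it for them, where the filtration subset allows. Rescaling the denominator alone would leave strip false positives in the numerator.
4. Base any statement about detecting all cases on that second estimate.

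The cost is wording, a further output from the existing simulation, and some added analysis; no new sampling is needed. The downsides are a wider interval, a possibly lower headline figure, and the assumption that test accuracy at baseline and endline also applies to the rounds between. The sensitive test has not yet been chosen, so its own accuracy will have to be stated once it is.
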